#### Conformity with CCM

We will be using the Assessment of Chronic Illness Care questionnaire (ACIC version 3.5), developed and validated by the McColl Institute to evaluate the organization of care in the FMG corresponding to each element of the CCM [18,20,21,72].

#### Changes in practice

A services evaluation grid will be completed with the administrator of the FMG in order to assess practice organization. Also, individual practice of participants will be assessed using clinical vignettes describing a patient presenting for a routine exam or for weight management. This tool was used in our previous study to demonstrate changes in reported management of obesity. A qualitative in-depth analysis of participants perceptions of the program will be performed using semi-structured interviews in each FMG [36]. This will increase our understanding of their experience, inter-professional collaboration, satisfaction with the program, change process and further identify and detail strengths and areas for potential improvement.

#### Evaluation of cost-effectiveness

We will thoroughly evaluate direct and indirect costs of implementation and delivery of our intervention, which are multiple: costs for the instigators of the program (using a log book for all team members involved in delivery of the intervention, etc.); costs for FMG professionals; costs for visits to other health care facilities where patients seek care for their specific problem of obesity/overweight; costs for patients; and costs to society modelized in a Markov model using data from the literature and the study [73,74]. Once data on all of those costs will be collected and compared between the two groups, a sensitivity analysis will be conducted with different scenarios over several years and with different discount rates to reflect the uncertainty of some variables [75].

#### *Quality Adjusted Life Years (QALYs*)

It is now recognized that to better treat the patient, and not only the disease, doctors should take into account the patient’s quality of life related to health. We will thus be using the most used questionnaire, the SF-36, derived from the “Medical Outcome Study” completed by patient-participants [76]. To address the most important limitations of the SF-36 and build an instrument that allows us to conduct a cost-effectiveness analysis, we will apply the transformation of Brazier et al. [77] to obtain QALYs based on stated preferences of individuals through the method of “Standard Gamble” (lottery). This transformation allows to take into account: 1) the existence of differences in individuals’ preferences between different dimensions of health, and 2) the possibility that the interval between different possible answers to each question in the SF-36 is not equal. The transformation model chosen will be model number 10 [78]. A complementary measure of QALYs will also be used to ensure consistency and continuity of results. This additional measure is to apply a time trade-off issue in the preferences of individuals [79]. This issue will be formulated as follows: “We make the assumption that for reasons that cannot be changed, you only have 10 years to live. Of these 10 remaining years to live, how many years of life would you be willing to give up to live the remaining years with a weight 20% less than what your weight is now?”

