### Aims of the study

#### Primary aims

Among patients who are regularly followed by a PCP for weight-related diseases targeted for lifestyle management (HTN, DM2 or IGT) and with a BMI ≥ 25 (*targeted diseases group*), we aim at improving, after 18 months of participation in our program (vs. control):the proportion of subjects who have an initial weight management intervention planned;the proportion of subjects who lose at least 5% of their initial weight;weight, waist circumference, lean body mass, blood pressure, physical fitness level, physical activity level and healthy eating habits;biochemical markers of metabolic control and cardiac risk (HbA1c, ApoA and ApoB).
Among patients who are regularly followed-up by a PCP for other health conditions (*regular follow-up group*), we aim at improving after 18 months of participation in our program (vs. control):the proportion of patients who have measured weight, BMI and waist circumference;the proportion of overweight or obese subjects who have an initial intervention planned;weight, waist circumference, lean body mass, blood pressure, physical fitness level, physical activity level, healthy eating habits and markers of metabolic control in overweight or obese subjects.

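### The time trade-off question is offered as a second QALY measure, but its alternative state is a 20% lower weight, not full health, so its score is not a QALY weight

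*Protocol article*

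**What the plan says.** The section Quality Adjusted Life Years (QALYs) of the protocol article describes two measures. The first is the SF-36, converted by a published transformation to a preference-based index built on standard gamble valuations. The article names this one as the instrument that makes a cost-effectiveness analysis possible.

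The second is introduced with "A complementary measure of QALYs will also be used to ensure consistency and continuity of results", and its method is named: "This additional measure is to apply a time trade-off issue in the preferences of individuals". The question is then given in full. The patient is to suppose that "you only have 10 years to live" and is asked "how many years of life would you be willing to give up to live the remaining years with a weight 20% less" than at present. The state on offer in exchange for lost years is "to live the remaining years with a weight 20% less than what your weight is now". Full or perfect health is not mentioned, and no scoring rule is given.

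Two patient groups are recruited. Under Primary aims, the targeted diseases group has "weight-related diseases targeted for lifestyle management (HTN, DM2 or IGT) and with a BMI ≥ 25". The other group is described as "Among patients who are regularly followed-up by a PCP for other health conditions", with no BMI criterion; the sample size section calls its 240 members unselected. The QALY section does not say which patients answer the item or at which visits.

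**The concern.** A time trade-off gives a QALY weight because the respondent trades years in the present state against fewer years in full health, whose utility is 1 by definition. Here the respondent trades against a lighter version of the present self. The answer shows how much the patient wants to weigh less, not how good or bad present health is on the scale from dead (0) to full health (1).

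The article calls the result a QALY measure and wants it to support the consistency of the results. If its level were set beside the SF-36 QALY, the two numbers would be on different scales. A gap between them would not show that either is wrong, and a match would not show that either is right. Used as a weight, the item would tend to make patients look healthier than they are, because they can have illness that a lower weight would not remove.

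**Working it through.** The documents give no time trade-off result, so there is no stated figure to reproduce. The check is the algebra of the question as worded.

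**Inputs from the article:** horizon of 10 years; alternative state at 20% below present weight; 22 × 10 = 220 targeted patients and 24 × 10 = 240 regular follow-up patients, 460 in all; patient evaluations at baseline and 18 months.

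**Assumptions:** the usual linear time trade-off model (dead = 0, no discounting) and the usual score, 1 − x/10, where x is the number of years given up. The utilities below are illustrative; the documents give none.

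**1. What the score measures.** At indifference,

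10 × U(now) = (10 − x) × U(lighter),

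so 1 − x/10 = U(now) / U(lighter), and U(now) = (1 − x/10) × U(lighter). Score and utility coincide only if U(lighter) = 1.

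**2. Size of the discrepancy.**

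| Years given up | Item score | U(now) if U(lighter) = 1.0 | 0.9 | 0.8 | 0.7 |
|---|---|---|---|---|---|
| 1 | 0.90 | 0.90 | 0.81 | 0.72 | 0.63 |
| 2 | 0.80 | 0.80 | 0.72 | 0.64 | 0.56 |

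For x = 2 the overstatement is 0, 0.08, 0.16 or 0.24. It is upward whenever U(lighter) is below 1.

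**3. Patients who would not trade.** With x = 0 the score is 1.00. This happens whenever the patient sees nothing worth trading life for in a lower weight, whatever the state of health.

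**4. Is U(lighter) = 1 plausible here?** The targeted group has hypertension, type 2 diabetes or impaired glucose tolerance, and the other group is followed for other conditions. The Background says moderate weight loss improves diabetes, blood pressure and lipids. Nothing says that a 20% loss brings full health, and no step values the lighter state separately.

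**5. Two conditional consequences.**

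- *If regular follow-up patients answer the item.* They are 240/460 = 52% of the planned sample and have no BMI criterion. A patient with BMI 22 would be asked to value 0.8 × 22 = 17.6. At BMI 25 the figure is 20.0.
- *If the item is given at both visits.* The reference follows the patient's weight. Someone who goes from 100 kg to 95 kg is asked about 80 kg first and 76 kg later. With assumed utilities, if U(now) rises from 0.75 to 0.80 and U(lighter) from 0.85 to 0.907, the score is 0.75/0.85 = 0.882 and then 0.80/0.907 = 0.882. A real gain would not show.

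**The case against.** The strongest reply is that the item has a minor role and that much of the possible harm depends on uses the article does not state. Most of this stands, and it rules out several stronger readings.

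- *That the cost per QALY will be wrong.* A reader might infer this from the label. But the article gives the cost-effectiveness role to the SF-36 transformation, and neither the costing text nor the QALY text puts the time trade-off into a ratio or into the Markov model.
- *That the item can never lead to a QALY weight.* The ratio could be multiplied by a separately measured utility of the lighter state. No such step is stated, so the criticism is of the item as written.
- *That comparison with the SF-36 index tells us nothing.* The article does not define the consistency it seeks. Comparing the direction of the difference between arms, or the ranking of patients, remains possible. Only agreement in level is ruled out.
- *That normal-weight patients will be asked, or that change over time is uninterpretable.* The article does not say who answers the item, and a restriction could sit in the questionnaire. The statement that evaluations take place at baseline and 18 months stands under the evaluation of patients, while the item stands under cost-effectiveness. No within-patient change analysis of it is described.

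It can also be said that a journal article leaves scoring to fuller documents. That does not remove the point. The question is given in full, and the missing full-health anchor lies in the question. A scoring rule alone cannot supply it without a value for the lighter state.

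**Conclusion.** The point holds in limited form. The item is described as a QALY measure, but as worded it measures preference for a 20% lower weight. Under the usual scoring it overstates the utility of current health whenever the lighter state falls short of full health: by 0 to 0.24 for a patient who gives up 2 years, over an assumed range of 1.0 to 0.7 for that state. Patients unwilling to trade score 1.00. Its level should not be used as a QALY weight or to confirm the level of the SF-36 QALY.

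This conclusion rests on the question's wording, the conventional score and the absence of any stated valuation of the lighter state. The sizes rest on assumed utilities. The concerns about normal-weight respondents and a shifting reference weight hold only if the item is given to all patients and at both visits; the article neither states nor excludes this. The reach is one complementary measure under secondary aim 5.

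**What to change.** **If the questionnaire is not yet in use:** reword the alternative so that the remaining years are lived in full health, and score the item as 1 − x/10. This changes one sentence and keeps a second QALY estimate.

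**If it is already in use:** rewording is too late for answers already collected. The ethics section describes consent and first patient contact in the past tense, so this may be the case. Then relabel the item as a weight-specific preference measure, report it descriptively in patients with BMI of at least 25, and state that it is neither a QALY weight nor a check on the level of the SF-36 QALY. If it was given at both visits, note beside the results that the reference weight moves with the patient's own weight.

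The second route costs a sentence or two of analysis text and the loss of a second QALY estimate. Neither route changes the primary outcomes, the sample size or the SF-36-based analysis.

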### Sample size, data analysis and interpretation

According to AIM 1, our primary variable of interest is the proportion of obese or overweight subjects with HTN, DM2 or IGT who will lose least 5% of their initial weight after eighteen months. Assuming that 30% drop-out or provide incomplete data, our study needs to recruit 220 obese or overweight subjects with HTN, DM2 or IGT in order to achieve 80% power (using chi-square) to detect a doubling in the proportion of those who will lose at least 5% of their initial weight, based on a proportion of 21% in the control group (which is the average proportion observed in the control groups of two of our previous studies) [32,33,67] and 42% in the intervention group (which represent half of the average benefits found in these two studies compared to control groups) (***AIM 1***). Similarly, 240 unselected patients provided 80% power (using Fisher’s-exact test because of small minimum expected cell size) to detect an improvement of the proportion of these patients who have a reported measure of BMI from 80% in the control group (based on reported practice in our previous participants) to 95% in the intervention group (which is close to the 100% recommended by the CCPGO) (***AIM 2***). For AIM 2, our primary variable of interest is the proportion of unselected patients who have a reported measure of BMI, which defines obesity according to WHO and is therefore essential for the screening of obesity.

The impact of our program on patient’s care will be assessed by the comparison of patients’ outcome variables between those recruited from FMGs allocated to intervention and those recruited from FMGs allocated to no intervention. Similarly, the impact of our program on PCPs will be determined by the comparison of variables related to PCPs between those who received the intervention and those who did not. Univariate analyses will use two-tailed unpaired *t* tests to compare continuous variables and chi-square or Fisher’s-exact tests to compare categorical variables. Continuous variables that are not normally distributed will be log-transformed in order to ascertain normal distribution, whenever possible, or will be compared using two-tailed Wilcoxon tests. Multivariate analyses will also be used in order to adjust for baseline differences between groups, potential confounders and cluster effects of individual FMGs. Should differences between patients’ or PCPs’ groups be evidenced, Pearson correlation analyses will be performed to determine if such differences are related to a potentially mechanistic variable. For example, benefits in patients’ outcome variables will be correlated with changes in variables assessing attitude, perceptions, knowledge and/or better clinical practice for their primary care providers. An α level of 5% will be used for all analyses.

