**Summary of design of the proposed research project.**

#### Study participants

The Integrated University Health Network, known as the RUIS (*Réseaux universitaires intégrés de santé*), of *Université de Sherbrooke* caters to a population of over 1 million people, encompassing a vast territory including Sherbrooke and Montérégie areas. A pool of at least 35 FMGs in this coverage area did not participate in our Phase-1 project. We will enroll a total of 10 of these FMGs in Phase-2, from which 4-10 members (including at least 2 PCPs and 1 nurse) will participate in our study. When we will initially contact FMGs, we will propose to them a study assessing lifestyle management in primary care and its evolution over time. When we will be in contact with 2 interested FMGs, we will randomize them to the intervention or control groups. The first FMG will then be offered to participate in our obesity management system with preceptorships and virtual learning community. The control FMG will be offered practice monitoring without being aware of the intervention. Participants of each group will sign different consent forms.

As much as possible, we plan to evaluate participants from FMGs pairs of intervention and control groups concomitantly in order to avoid bias related to time of evaluation (due to seasonal effects on weight, campaigns of health promotion, high-impact scientific publications, etc.). Within each FMG, adult patients who present for follow-up will be offered by FMG clerical personnel to have their chart accessed by our team and to be contacted if eligible for the project. If they consent, their chart will be screened to verify if they had, during the past 2 years, at least 4 documented visits for the targeted disease group and at least 2 visits for the regular follow-up group, and if continued follow-up is planned or highly probable in the next 18 months. We aim to include in our study 22 patients per FMG in the targeted disease group, and 24 patients per FMG in the regular follow-up group (total of 460 patients). Patient numbers will be prospectively accrued within each patient category during the recruitment period and before preceptorship delivery for the intervention group, until targeted numbers are achieved. In order to minimize important potential biases, patients will be kept blinded regarding their FMG group and the study objectives related to the evaluation of this intervention.

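### The 80% power for both primary variables is computed as if patients were randomised, although ten FMGs are; Aim 1 falls short at almost any positive ICC, Aim 2 depending on attrition and ICC

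*Protocol article*

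**What the plan says.** The unit of randomisation is the FMG. The Study participants section states "When we will be in contact with 2 interested FMGs, we will randomize them to the intervention or control groups", and the number of clusters is fixed there too: "We will enroll a total of 10 of these FMGs in Phase-2". Each contributes "22 patients per FMG in the targeted disease group, and 24 patients per FMG in the regular follow-up group (total of 460 patients").

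The section on sample size, data analysis and interpretation then sizes both primary variables at patient level. For Aim 1 (loss of at least 5% of initial weight), it states that "our study needs to recruit 220 obese or overweight subjects with HTN, DM2 or IGT in order to achieve 80% power (using chi-square"). The allowance for loss reads "Assuming that 30% drop-out or provide incomplete data". The control rate reads "based on a proportion of 21% in the control group", and the target rate for the other arm reads "42% in the intervention group (which represent half of the average benefits found in these two studies compared to control groups"). For Aim 2 (a reported BMI measure): "240 unselected patients provided 80% power", by Fisher's exact test, for 80% against 95%.

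The section states no intracluster correlation, design effect or allowance for the number of FMGs. Its analysis paragraph compares arms with t, chi-square or Fisher tests and mentions FMG clustering only as one adjustment in the multivariate analyses.

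**The concern.** Patients of one FMG share clinicians, nurses and local habits, and the intervention is delivered to the FMG. Their outcomes can be expected to correlate, so 22 patients from one practice carry less information than 22 independent patients. With five FMGs per arm, the between-practice variance is also estimated from few units, which costs further power under a small-sample reference distribution. A chi-square or Fisher calculation sees neither effect.

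At stake is how the result will be read. The article says that findings will inform health-system decisions and that smaller benefits than expected would lead to changes in the programme. Someone who takes 80% at face value would give a non-significant result more weight than this design supports.

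**Working it through.** **Inputs from the protocol.** 10 FMGs, 5 per arm; 22 and 24 patients per FMG; Aim 1: 220 recruited, 30% loss, 21% vs 42%; Aim 2: 240 patients, 80% vs 95%; alpha 5%, taken as two-sided.

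**Assumptions added here.** ICC 0.01 to 0.10 (the document gives none); equal evaluable numbers per FMG; for Aim 2, both 30% loss and no loss.

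**Step 1: reproduce the stated figures.**
- Aim 1: the two-proportion formula with pooled variance needs 76 per arm, 152 in all, and 152/0.7 = 218, against the stated 220. Conversely, 220 × 0.7 = 154, or 77 per arm, gives 80.7% by formula and 81.0% by exact enumeration of the chi-square test. The design effect is therefore exactly 1, with about one point of power to spare.
- Aim 2 with 30% loss: 240 × 0.7 = 168, or 84 per arm; Fisher enumeration gives 81.7%.
- Aim 2 without loss: 120 per arm; Fisher enumeration gives 93.5%.

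**Step 2: add clustering.** With m evaluable patients per FMG:
- DEFF = 1 + (m − 1) × ICC
- effective n per arm = 5m / DEFF
- SE = √{[p1(1 − p1) + p2(1 − p2)] / effective n}
- λ = |p1 − p2| / SE
- power = Φ(λ − 1.96) with a normal reference, or from the noncentral t with 10 − 2 = 8 df (critical value 2.306)

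Example, Aim 1 at ICC 0.02: m = 154/10 = 15.4; DEFF = 1 + 14.4 × 0.02 = 1.288; effective n = 77/1.288 = 59.8; SE = √[(0.1659 + 0.2436)/59.8] = 0.0828; λ = 0.21/0.0828 = 2.54. Power is 72% (normal) or 61% (8 df).

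| Variable | m | ICC | DEFF | Normal | t, 8 df |
|---|---|---|---|---|---|
| Aim 1 | 15.4 | 0.01 | 1.144 | 77% | 66% |
| Aim 1 | 15.4 | 0.02 | 1.288 | 72% | 61% |
| Aim 1 | 15.4 | 0.05 | 1.720 | 59% | 49% |
| Aim 2, 30% loss | 16.8 | 0.02 | 1.316 | 75% | 64% |
| Aim 2, 30% loss | 16.8 | 0.05 | 1.790 | 62% | 51% |
| Aim 2, 30% loss | 16.8 | 0.10 | 2.580 | 47% | 38% |
| Aim 2, no loss | 24 | 0.02 | 1.460 | 85% | 74% |
| Aim 2, no loss | 24 | 0.05 | 2.150 | 69% | 58% |
| Aim 2, no loss | 24 | 0.10 | 3.300 | 51% | 42% |

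The normal column uses the unpooled variance. The pooled chi-square form gives slightly less, for example 75%, 70% and 57% for Aim 1.

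**Step 3: where 80% is lost.** Aim 1, normal reference: at an ICC of about 0.001 (pooled) or 0.004 (unpooled); on 8 df power is 71% even at ICC 0. Aim 2 with 30% loss: at about 0.007 (pooled) or 0.010 (unpooled); on 8 df power is 75% at ICC 0. Aim 2 with no loss: at about 0.026 (pooled) or 0.029 (unpooled), or about 0.012 on 8 df.

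**Step 4: detectable difference, Aim 1, 8 df.** Solving for 80% power against 21% in the control arm gives 46.1% at ICC 0.01, 47.7% at 0.02 and 51.8% at 0.05.

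**The case against.** Several counter-arguments deserve weight.

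*Aim 2 may not lose 30%.* The loss is stated for Aim 1 only, and the Aim 2 sentence is joined to it just by the word similarly. BMI recording is assessed from charts, so a patient who misses the 18-month visit may still be analysable. This stands. A reader might infer that 80% is certainly missed for both primary variables. The documents do not support that: without loss, Aim 2 keeps 80% at a small ICC. The 30% reading fits the stated 80% better, but it is an inference.

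*The 8-df figures depend on a test that the protocol does not name.* This also stands, which is why both references are shown. The drop below 80% at ICC 0 comes from that reference alone. Analysing the FMG pairs would leave 4 df; pairing could recover some power if the matching works, but the plan claims no such gain.

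*The analysis adjusts for cluster effects.* This does not rescue the power. An analysis that respects clustering has less power than the tests used for sizing. An unadjusted chi-square test would instead have a true level of about 2[1 − Φ(1.96/√DEFF)] = 6.7%, 8.4% and 13.5% for Aim 1 at ICC 0.01, 0.02 and 0.05.

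*An article condenses the full plan.* The calculation here is shown with its inputs and reproduces without any clustering term, so nothing in it points to an allowance held elsewhere.

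*The consequence can be overdrawn.* A reader might infer that a null result would be taken as proof against the programme. The article speaks only of modifying it.

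**Conclusion.** Wrong as written. The arithmetic is right for the tests named, but those tests assume a design that the trial does not have.

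For Aim 1 the 80% holds only with essentially no correlation within FMGs. It becomes 59% to 77% (normal reference) or 49% to 66% (8 df) over an assumed ICC of 0.05 down to 0.01. For Aim 2 the conclusion is conditional. With 30% loss, power is 47% to 75% (normal) or 38% to 64% (8 df) over ICC 0.10 down to 0.02. With all 240 charts, it is 51% to 85% or 42% to 74%.

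The size rests on assumed ICCs, equal evaluable numbers per FMG and the choice of reference distribution. That a positive ICC lowers power below the independent-patient figure rests on none of these. It would be too strong to say that the trial has an even chance of detecting its Aim 1 target: that holds only at ICC 0.05 on 8 df.

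**What to change.** In the sample size section, replace both 80% statements with cluster-based power at the planned size of five FMGs per arm. Declare the ICC range as an assumption, with its source if the sponsor has one, and name the cluster-respecting analysis to which the power refers, including its reference distribution. Show Aim 2 with and without the 30% loss, and say which applies. Add the detectable difference for Aim 1: on 8 df, 80% power needs 21% against about 46% to 52% for ICC 0.01 to 0.05. Stop citing chi-square and Fisher's exact tests as the basis of power.

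The change is wording and a short calculation. It asks for no extra patients or FMGs. Its cost is a less favourable stated power.

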#### Secondary aims

3.Among health professionals who receive the intervention (vs. those who did not), we aim at:ameliorating their attitudes and perceptions towards patients and treatment effectiveness;improving their perception of self-efficacy in managing obesity;increasing their knowledge and expertise on obesity management; andchanging their practice.
4.Among patients who are followed by PCPs (both targeted disease and regular follow-up groups) who receive the intervention (vs. control), we aim at:evaluating their attitudes and perceptions regarding obesity/overweight and lifestyle; andimproving their satisfaction regarding their management.
5.Evaluate costs and indicators of cost-effectiveness of the intervention.6.Transfer knowledge to intervening parties and decision-makers of the health system using embedded knowledge transfer to patients, health professionals and decision-makers in addition to traditional end-of-grant strategies.

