#### Evaluation of health professionals (PCPs and nurses)

All evaluations will take place at baseline, T1 (1 month after the preceptorship for the intervention group and 1 month after baseline for the control group) and 12 months after T1 in order to compare the data collected during our Phase 1 study and to compare intervention and control groups. The same questionnaires that we developed and validated will be used to evaluate Aim 3 of this proposal. We have slightly modified some tools based on the results of our Phase 1 project. Results will be correlated to patients’ outcome.

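### Aim 3 and the analysis section group health professionals by receipt of the intervention; the comparison should follow the allocation of their FMG

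*Protocol article*

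**What the plan says.** Three places in the protocol article define how health professionals are compared, and they do not agree.

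- **Secondary aims, Aim 3:** "Among health professionals who receive the intervention (vs. those who did not". This is receipt.
- **Sample size, data analysis and interpretation:** the effect on PCPs is to be judged by comparing "variables related to PCPs between those who received the intervention and those who did not". This is receipt again. The sentence before it, on patients, compares "those recruited from FMGs allocated to intervention and those recruited from FMGs allocated to no intervention", which is allocation.
- **Evaluation of health professionals (PCPs and nurses):** the assessments are made "to compare intervention and control groups". This is group.

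The unit of randomisation is the FMG, in pairs: "When we will be in contact with 2 interested FMGs, we will randomize them to the intervention or control groups". The programme comes afterwards, as an offer: "The first FMG will then be offered to participate in our obesity management system with preceptorships and virtual learning community". The Intervention section describes two training days about a month apart, monthly virtual meetings, a web site and forum, and coaching every three months. Control FMGs are given only copies of guidelines. The article does not say which of these components a professional must take up to count as having received the intervention, or how an enrolled professional who takes up little or none is classified.

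**The concern.** Allocation is fixed by randomisation. Receipt is behaviour that follows it. If the groups are formed by receipt, an enrolled professional in an intervention FMG who does not take part is no longer counted in the intervention group. That person is either counted with the controls or left out.

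The outcomes in Aim 3 are attitudes, perceived self-efficacy, knowledge and practice in obesity care. It is plausible, though the article does not state it, that professionals who attend obesity training differ on these from those who do not. A receipt-based comparison could then show a difference even if the programme had no effect. At stake is whether the results for professionals rest on the randomised comparison, as the patient results do.

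**Working it through.** **No plan figure to reproduce.** The two stated sample sizes (220 and 240) are for patient outcomes, which are compared by allocation. The article gives no sample size, power or expected effect for professionals.

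**Where receipt and allocation can differ.** Control FMGs have no route to the programme, so the two groupings differ only for enrolled members of intervention FMGs who do not take it up. Each of 10 FMGs contributes members as follows: "from which 4-10 members (including at least 2 PCPs and 1 nurse) will participate in our study". That is 10 × 4 = 40 to 10 × 10 = 100 professionals. Randomisation in pairs puts five FMGs in each arm, so 20 to 50 professionals per arm. Non-attendance of 10% would mean 2 to 5 people, and 30% would mean 6 to 15.

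**Size of the bias if the rule is followed literally.** The assumptions, none of which comes from the article, are:

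- arms of equal size and no true effect, so both arm means are 0
- a fraction *f* of the intervention arm does not attend
- attenders score *d* SD higher than non-attenders at outcome
- non-attenders are counted as non-recipients, together with the controls

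Then:

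- mean of attenders = *f d*
- mean of non-attenders = −(1 − *f*) *d*
- mean of non-recipients (controls plus non-attenders) = −*f*(1 − *f*) *d* / (1 + *f*)
- spurious difference = *f d* + *f*(1 − *f*) *d* / (1 + *f*) = 2*f d* / (1 + *f*)

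Example with *f* = 0.2 and *d* = 0.5: attenders +0.10, non-attenders −0.40, non-recipients 0.2 × (−0.40) / 1.2 = −0.067. The difference is 0.10 + 0.067 = 0.167 SD.

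| *f* | *d* = 0.3 | *d* = 0.5 | *d* = 0.8 |
|---|---|---|---|
| 0 | 0 | 0 | 0 |
| 10% | 0.055 | 0.091 | 0.145 |
| 20% | 0.100 | 0.167 | 0.267 |
| 30% | 0.138 | 0.231 | 0.369 |

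If non-attenders were left out and not counted with the controls, the spurious difference would be *f d*. That is 0.10 SD in the example, and 0.1 × 0.3 = 0.03 to 0.3 × 0.8 = 0.24 SD over the same range.

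**The case against.** The strongest reply is that the authors use receiving the intervention as shorthand for being allocated to it.

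- The abstract describes FMGs as randomised to receive the programme.
- Aim 4 refers to patients of PCPs who receive the intervention, set against control, and the analysis section then compares patients by allocation.
- The disputed sentence opens with *Similarly*, straight after the allocation rule for patients, which suggests the same comparison.
- The section on evaluating professionals speaks of two groups and times the T1 assessment by those groups.

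This stands as evidence of intent. It does not settle the rule, because the only grouping stated for professionals in the analysis section is receipt, and Aim 3 repeats it.

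It is also fair to say that the article gives no attendance figures, that voluntary attendance is inferred from the programme being offered, and that the bias figures rest wholly on assumption. How partial attenders enter analysis sets could be left to a fuller document. The choice between receipt and allocation is different, because the article states it.

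Two stronger readings are tempting, and the article supports neither.

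- A reader might infer that randomisation is broken for every professional outcome. Nothing in the text moves non-attenders into the comparator. With full uptake the two comparisons are identical, and FMG-level measures such as the services grid are less exposed.
- A reader might infer that the bias passes into the correlations between professionals' changes and patients' outcomes. Those correlations use each provider's own scores, which do not change with the grouping. At most, a spurious group difference could prompt that analysis to be run.

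**Conclusion.** The point holds as an inconsistency with a conditional consequence. Aim 3 and the analysis section group professionals by receipt, while the evaluation section groups them by arm and patients are grouped by FMG allocation. Allocation may be what is meant. Taken literally, the receipt rule is an as-treated comparison that can bias individual-level professional outcomes when uptake in intervention FMGs is incomplete.

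The size cannot be derived from the article. The illustration gives about 0.055 to 0.37 SD under assumed non-attendance of 10 to 30% and an assumed gap of 0.3 to 0.8 SD. It requires no true effect, equal arms and non-attenders counted as non-recipients, and it is zero at full attendance. Only secondary aims are affected. The primary patient comparisons are already defined by allocation.

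**What to change.** In Aim 3 and in Sample size, data analysis and interpretation, replace the receipt wording with one rule, for example: *All enrolled professionals, PCPs and nurses, will be compared according to the arm to which their FMG was randomised, whatever part of the programme they attended, with adjustment for clustering by FMG.* The analysis sentence now names PCPs only, whereas Aim 3 covers health professionals, so the new wording should cover both.

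If a receipt-based comparison is wanted, label it supplementary, define in advance what counts as receipt, and report it with attendance by component.

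The cost is wording only. No extra participants or measurements are needed, and the cluster adjustment is already among the planned multivariate analyses. If uptake is incomplete, the estimated effect may be somewhat smaller, because it then reflects the programme as offered to the FMG.
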